### Participants

In this RCT, a minimum of 40 office-workers aged 40–64 years will be recruited, enrolled, and randomized (n = 20 per group). Potential eligible subjects will be recruited from two office companies in Coimbra city, Portugal. The principal investigator (PI) of this project will meet with the directors/leaders of these companies to present and discuss the purposes and procedures of this research project. Afterwards, a poster will be disseminated on their internal web pages and the subjects will be able sign up online or by telephone. Interested subjects will receive information about the study and will be pre-screening for initial eligibility criteria through telephone/online interviews. The subjects ruled eligible will be invited for an in-person screening visit where they learned more about the study, sign the informed consent form, and complete additional screening measures. Lastly, the subjects that meet all the defined eligibility criteria will be invited to return for a baseline assessment visit. After the baseline assessments, participants will be randomized and notified by email/telephone (by the PI).

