**Inclusion Criteria**
Men and women between 40 to 64 years old
Physically inactive adults (not meeting the Global recommendations on physical activity for health [50, 51])
Full-time workers with sedentary occupations (report spend ≥65% of their workday in activities with low energy expenditure i.e., 1.5 METs or lower);
Body mass index between 18 and 29.9 kg/m^2^
Willingness to maintain the current nutrition pattern and to participate in all testing assessments

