### Randomization

Participants who meet all eligibility criteria will be randomly assigned to either control or experimental group with a 1:1 allocation as per a computer random number generator. Permuted block randomization will be used to ensure an equal sample size in the two groups. The block sizes will not be divulged to ensure concealment. This randomization process will be generated by an independent biostatistician. The study participants will be enrolled and assigned to their respective groups by the PI. The experimental group will perform 16-weeks of CT exercise and the control group will maintain their usual habits, including not participating in any exercise program.

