*Assessment of dietary intake*. Dietary habits will be assessed using a semi-quantitative Food Frequency Questionnaire (FFQ) [98], based on the previous 12 months. The FFQ was previously adapted for the Portuguese population [99, 100]. This instrument contains 82 food items, including 9 possible frequency responses, ranging from “never” to “six or more times per day” [100]. Any foods not reported in the FFQ but eaten regularly can be registered in an open-ended section [100]. To obtain nutrient intake, the frequency of consumption of each food item will be multiplied by the respective standard average portion (in grams), and by a seasonal variation factor for food consumed in specific seasons (0.25 are considered the average seasonality of three months) [100]. The conversion of food into nutrients will be performed using the software program Food Processor Plus (version 5.0, ESHA Research, Salem, OR), based on values from the US Department of Agriculture and from the composition of typical Portuguese foods that were included in this software [100, 101].

*Health*, *demographic*, *and lifestyle data*. Sociodemographic characteristics such as chronological age, gender, education degree, and marital status will be collected to characterize the sample and to adjust models. Health information will include past and current diseases (acute and/or chronic), medication, family history of metabolic diseases, dementia, or cognitive impairment. The “Pittsburg Sleep Quality Index” (PSQI) questionnaire will also be applied, before and after the trial, to assess subjective sleep quality over the previous month [102, 103]. Lifestyle information will include smoking history, consumption of alcoholic drinks, substance abuse and supplement use.

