### Data analysis

Data analyses will be performed using SPSS Statistics version 25.0 (SPSS Inc., IBM Company, Chicago, Illinois, USA). Descriptive statistics (mean ± SD) will be performed for all variables in the analysis. The assumption of normality will be tested using histograms, normal probability plots and Shapiro-Wilk test. Chi-squared test will be performed to analyse sex proportions between groups. Assuming data normality, a two-way analysis of variance (ANOVA) for repeated measures will be applied for intra- and inter-group comparisons. In absence of normality, non-parametric Kruskall-Wallis test will be used. Bonferroni’s *post hoc* test will be performed if significant differences exist (alpha level set at 0.05). The magnitude of the global effect size will be calculated using Cohen’s effect size [104]. The Cohen’s d effect size is categorized according to the following criteria: *d* = < 0.20 (small), 0.21–0.79 (medium) and > 0.80 (large) [104]. The bivariate associations between the changes promoted by the exercise program and the different variables studied will be assessed by Spearman’s rank and Pearson’s coefficients. The strength of the associations will be classified as follows [105]: very high (0.90 < r < 1.00); high (0.70 < r < 0.90); moderate (0.50 < r < 0.70); low (0.30 < r < 0.50); little (0.10 < r < 0.30). Significance level set at *p* ≤ 0.05.

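### Covariates are collected for model adjustment but no planned analysis contains one, and the only step on sex is an uninformative chi-squared test between arms

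*Protocol article*

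**What the plan says.** Both sexes are eligible (Table 1: "Men and women between 40 to 64 years old"). The Randomization section describes allocation "with a 1:1 allocation as per a computer random number generator" and gives the purpose of the blocks: "Permuted block randomization will be used to ensure an equal sample size in the two groups". It names no stratification factor. Participants are "recruited from two office companies in Coimbra city, Portugal".

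Under Supportive measures, in the paragraph on health, demographic and lifestyle data, age, gender, education and marital status "will be collected to characterize the sample and to adjust models".

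The Data analysis section then sets out the analyses. For sex: "Chi-squared test will be performed to analyse sex proportions between groups". For the outcomes, if normality holds, "a two-way analysis of variance (ANOVA) for repeated measures will be applied for intra- and inter-group comparisons"; otherwise, "In absence of normality, non-parametric Kruskall-Wallis test will be used". Bonferroni post hoc tests and bivariate correlations complete the list. No covariate appears in any of them.

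**The concern.** One section announces adjustment; the section that defines the analyses has no model in which it could take place. The Kruskal-Wallis fallback cannot take a covariate at all. A reader cannot tell whether the treatment comparison will be adjusted, or for which of four candidate variables. The trial has many primary outcomes, so the choice would be left open for each of them.

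The one stated step on sex does not fill the gap. A significance test of sex between randomised arms asks whether chance produced the difference, and randomisation has already answered that. Whether adjustment is useful depends on how strongly sex predicts the outcome, which the test does not address. In a trial of this size, sizeable sex differences between arms are common and the test will usually be silent about them. At stake are the precision of the arm comparison and its interpretation when the arms happen to differ in sex.

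**Working it through.** **Inputs.** From the protocol article: 20 per arm (40 in total), 20% more to be enrolled for dropout (48, or 24 per arm), 1:1 allocation, no stratification factor named. Assumed, because the article gives neither: half the participants are women; sex shifts the change score by δ = 0.5 or 1.0 within-sex SD. The plan states no figure of its own on this point, so there is none to reproduce.

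**Step 1: how often the arms differ.** The number of women in one arm, X, is treated as hypergeometric (40 people, 20 women, 20 per arm). This ignores the block structure. The difference in women between arms is 2X − 20.

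| Difference in women | Example | Probability | Pearson χ² (uncorrected) | p |
|---|---|---|---|---|
| 4 or more | 12 v 8 | 0.343 | 1.6 | 0.21 |
| 6 or more | 13 v 7 | 0.113 | 3.6 | 0.058 |
| 8 or more | 14 v 6 | 0.026 | 6.4 | 0.011 |

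Probabilities are for the stated difference or a larger one; χ² and p are for the example. With equal margins χ² = N × d², where d is the difference in the proportion of women: 40 × 0.3² = 3.6 and 40 × 0.4² = 6.4. The test therefore flags only 14 v 6 or worse, 2.6% of allocations.

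**Step 2: sensitivity.** With 30% or 70% women at 20 per arm, a gap of 20 percentage points or more has probability 0.30, and the test flags from a 30-point gap (8.2% of allocations). At 24 per arm with half women, a difference of 4 or more women has probability 0.387 and of 6 or more 0.148; 15 v 9 gives χ² = 48 × 0.25² = 3.0, p = 0.083, not flagged. In percentage points the gaps shrink as the trial grows: at 24 per arm a gap of 20 points or more has probability 0.15, against 0.34 at 20 per arm.

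**Step 3: what adjustment gains on change.** In units of the within-sex variance, at 20 per arm:

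- Var(d) = 1/39 = 0.0256.
- Unadjusted variance of the arm difference = 2/20 + δ² × 0.0256. This is 0.1064 at δ = 0.5 and 0.1256 at δ = 1.0.
- Adjusted for sex = (2/20) × E[1/(1 − d²)] = 0.1 × 1.028 = 0.1028.
- Ratio adjusted/unadjusted = 0.1028/0.1064 = 0.97 at 0.5 SD and 0.1028/0.1256 = 0.82 at 1.0 SD.
- With a sex-stratified list as well, ideally balanced: 0.1/0.1064 = 0.94 and 0.1/0.1256 = 0.80.

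The saving from adjustment is thus about 3% at 0.5 SD and 17–18% at 1.0 SD.

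**Step 4: what an imbalance does in one realised trial.** The shift in the arm contrast is d × δ. For gaps of 20 to 30 points and assumed sex effects on change of 0.3 to 0.8 SD, it runs from 0.2 × 0.3 = 0.06 SD to 0.3 × 0.8 = 0.24 SD.

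**Step 5: where it enters.** The group-by-time contrast of the repeated-measures ANOVA removes any sex difference in level that is constant over time; only a sex effect on change remains. The between-group main effect does carry level differences. So would the Kruskal-Wallis test if applied to raw values; the article does not say whether it is applied to levels or to changes.

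**The case against.** The strongest reply is that this is a condensed article, that naming covariates is normal analysis-plan content, and that the Supportive measures section does state an intention to adjust. That stands as far as it goes: the absence of a covariate list alone would be no finding. But the Data analysis section goes further than silence. It names specific procedures, none with a covariate and one unable to take any, and fixes a test of sex that informs nothing.

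A reader might infer that sex imbalance is neither prevented nor corrected and so biases the trial. The documents do not support that. Under valid randomisation a chance imbalance neither biases the estimator nor inflates type I error, and unstratified permuted blocks are an acceptable design. The stated intention to adjust also counts against so absolute a claim. Nor does the text tie adjustment to the chi-squared result; choosing covariates after seeing it is left possible, not planned.

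A reader might also point to fat mass, grip strength, lung volumes or leptin as outcomes that differ between men and women. A difference in level drops out of the group-by-time contrast, and percent-predicted spirometry is already standardised for age and sex. The gain on change is small unless sex strongly affects change, and the documents give no figure for that effect.

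One point runs the other way. Combined-training participants attending fewer than 80% of sessions are left out of the analysis, so sex imbalance in the analysed set need not be pure chance. The documents give no figures from which to size this.

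**Conclusion.** The point holds as a mismatch between two sections together with a badly chosen test; it is no threat to the validity of the randomised comparison. The loss is in precision and in conditional imbalance: modest for the group-by-time contrast (about 3% of variance at a 0.5 SD sex effect on change, 17–18% at 1.0 SD), and potentially larger for between-group comparisons of levels and for a Kruskal-Wallis fallback applied to levels. The imbalance probabilities rest on an assumed 50% share of women and change little between 30% and 70% for a 20-point gap. The variance figures rest on the assumed sex effects. The sample-size figure is not affected. The correction is worth making because it is cheap and uses data already collected.

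**What to change.** 1. Reconcile the two sections. In Data analysis, fix sex and age in advance as covariates in the between-arm model for each outcome.
2. Under Supportive measures, state that education and marital status describe the sample and are not used for the treatment comparison.
3. Replace the chi-squared test with a descriptive report of sex by arm.
4. If randomisation has not started, have the independent biostatistician generate the permuted-block list separately for men and women. Stratifying by company as well is not advised with about 40 participants: the added strata work against equal arm sizes.

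**Cost.** A few lines of text and, under item 4, a new computer list. Adjustment uses one or two residual degrees of freedom. For outcomes that sex and age do not predict, the expected loss of precision is roughly 1/39 to 2/39, or about 2–5%. Incomplete blocks in two strata may leave a small imbalance in arm totals; its size cannot be given because the block sizes are not disclosed.

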## Materials and methods

### Study design and setting

This trial is designed as a single-blinded two-arm randomized controlled trial (RCT) with parallel groups, and an allocation ratio of 1:1. Fig 1 illustrates the overall study. This study protocol follows the SPIRIT Statement guidelines for standard protocol items in clinical trials [46] and is registered in the Clinicaltrials.gov ID: NCT04868240 (date of registration April 30, 2021). This RCT study has been designed and results will be reported according to the Consolidated Standards of Reporting Trials (CONSORT) statement [47]. Furthermore, and since that exercise training interventions are not properly and completely addressed by the CONSORT checklist [48], the guidelines of the Consensus on Exercise Reporting Template (CERT) will also be considered [49].

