### Estimated sample size

The sample size was calculated using a priori power analysis through the G*Power software version (3.1.9.2.), following the guidelines of Faul et al. [54]. For an effect size of 0.30, a sample size of 20 participants per group achieves 95% power to detect differences among the means versus the alternative of equal means using an F test with a 5% α-level. This analysis indicated a minimum total sample size required in this study. We plan to enrol 20% more persons to account for dropouts.

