### Outcome measures

This trial includes a screening and baseline assessment period of 20 days (four visits), a 16-week CT program period, and a mid-testing and post-testing period of 3 (one visit) and 10 days (two visits), respectively. On the first visit, subjects will sign the informed consent form and will complete additional screening measures. Subjects that meet all eligibility criteria will be enrolled and complete a set of outcome measures over visits 2 and 3. After the baseline assessments, subjects will be randomly assigned to either control or experimental group, and the participants of the experimental group will carry out the evaluations of 10RM (Visit 4). The exercise sessions will be performed over 16-weeks on a single site and supervised by two instructors. Baseline assessments will be repeated after 8 weeks (mid-testing, visit 5) and upon completion of the intervention (visits 6 and 7). Importantly, we will consider the phase of the menstrual cycle in non-menopausal women (i.e., menstrual phase, follicular phase, ovulation phase and luteal phase), taking baseline and follow-up evaluations at the same time of the cycle. A timetable of the enrolment, intervention and assessments are presented in Table 3.

**Table 3 pone.0263455.t003:** Schedule of enrolment, interventions, and assessments.

	STUDY PERIOD							
	Baseline				Intervention	Follow-ups		
Timepoint	Visit 1^a^	Visit 2^a^	Visit 3^a^	Visit 4^a^	Sessions 1–48^b^	Visit 5^c^	Visit 6^d^	Visit 7^d^
Day number	-20 to -15	-15 to -10	-10 to -5	-5 to -1	1 to 112	56 to 58	113 to 118	118 to 123

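### The planned repeated-measures ANOVA leaves out the baseline value as a covariate and does not name the treatment test, which costs precision and clarity but not validity

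*Protocol article*

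**What the plan says.** Under Data analysis, if the data are normal, "a two-way analysis of variance (ANOVA) for repeated measures will be applied for intra- and inter-group comparisons". Bonferroni post hoc tests follow a significant result, and Kruskal-Wallis replaces the ANOVA when normality fails. The section does not single out the group-by-time interaction as the treatment test, does not define a between-group estimate, and does not mention the baseline value of the outcome as a covariate.

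Under Outcome measures, eligible subjects "complete a set of outcome measures over visits 2 and 3" and are randomised afterwards. Table 3 marks a pre-randomisation assessment for every primary and secondary outcome. It gives three time points for body composition, fitness, lung function, quality of life and blood pressure. It gives two for blood and saliva, with no sample at week 8.

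Under Supportive measures, sociodemographic data "will be collected to characterize the sample and to adjust models".

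Under Estimated sample size: "For an effect size of 0.30, a sample size of 20 participants per group achieves 95% power to detect differences among the means", "using an F test with a 5% α-level". The correlation between repeated measures is not stated.

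**The concern.** Two things are at stake.

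- **Precision.** With two time points, the interaction F test is a comparison of mean changes between groups. It subtracts the whole baseline value, whereas ANCOVA subtracts only the part that predicts the follow-up value. ANCOVA is therefore more precise for any correlation below 1. The baseline values are already being collected, so a trial of about 40 people would give up this precision for nothing.
- **An unnamed contrast.** A two-way repeated-measures ANOVA yields a group effect, a time effect and an interaction. The article speaks only of intra- and inter-group comparisons. If the group main effect were taken as the inter-group comparison, it would average in the baseline, where randomisation means no treatment effect can exist. With three visits, the interaction is a two-degree-of-freedom test across all visits. It does not by itself give the week-16 difference.

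**Working it through.** **Step 1: the plan's own figure.** Inputs from Estimated sample size: effect size 0.30, N = 40, alpha 0.05, power 95%. Assumed: the effect size is Cohen's f, m = 2 time points, r = 0.5. For the interaction in a repeated-measures ANOVA:

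λ = f²·N·m/(1−r) = 0.09 × 40 × 2/0.5 = 14.4, with 1 and 38 degrees of freedom. Power is 0.959, and the smallest even N for 95% is 40.

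The stated size is reproduced. Other readings of f = 0.30 do not give 40: the three-visit interaction at r = 0.5 needs 32, the group main effect at m = 2 and r = 0.5 needs 112, and a one-way ANOVA needs 148. The implied difference in change D, in SD units, solves λ = D²·(N/4)/[2(1−r)], so D² = 14.4 × 4/40 = 1.44 and D = 1.2 SD.

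**Step 2: variances.** With equal SDs at both time points, the per-person variances behind the group difference, in units of σ², are:

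- change score (group-by-time): 2(1−r)
- ANCOVA: 1−r²
- ratio of ANCOVA to change score: (1+r)/2, which is 0.65, 0.75, 0.85 and 0.95 at r = 0.3, 0.5, 0.7 and 0.9

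**Step 3: power.** Noncentral t with noncentrality D/√(v·2/20), where v is the variance above, and 38 (change) or 37 (ANCOVA) degrees of freedom. The 0.6 SD effect and every r are assumptions. Example at r = 0.5: 0.6/√(1.00 × 0.1) = 1.897 for change and 0.6/√(0.75 × 0.1) = 2.191 for ANCOVA.

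| Effect | r | Change score | ANCOVA |
|---|---|---|---|
| 0.6 SD | 0.3 | 34.6% | 49.1% |
| 0.6 SD | 0.5 | 45.6% | 56.9% |
| 0.6 SD | 0.7 | 66.5% | 73.5% |
| 0.6 SD | 0.9 | 98.5% | 98.9% |
| 1.2 SD (implied by the plan) | 0.5 | 95.9% | 98.9% |

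These figures ignore the small cost of chance baseline imbalance. A simulation at 0.6 SD and r = 0.5 gave 0.460 and 0.560, a gain of 10 points instead of 11.

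**Step 4: the group main effect, if it were used.** Averaging baseline with follow-up halves the effect to D/2, and the variance of the average is (1+r)/2. At 0.6 SD and r = 0.5 the noncentrality is 0.3/√(0.75 × 0.1) = 1.095 and power is about 19%. At 1.2 SD it is about 57%.

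**The case against.** The strongest reply is that nothing here is wrong in the strict sense. In a randomised trial the group-by-time test is unbiased, and with two time points it already uses the baseline. The sample size reproduces as exactly that interaction, which suggests that it is the intended test. At the plan's implied effect, adjustment adds only 3 points of power. All of this stands.

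Four stronger readings are tempting, and the article does not support them.

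- **That efficacy will be claimed from within-group tests.** The article puts intra- and inter-group comparisons under one ANOVA. A claim resting on a significant change in one arm only is a prediction about reporting, not something the plan states.
- **That Supportive measures contradicts Data analysis.** Adjustment is stated as intended, a repeated-measures ANOVA can take covariates, and the covariate list may sit in an analysis plan that is not shown.
- **That a new model rescues participants throughout.** For blood and saliva, someone without the week-16 sample is lost under either method. For three-visit outcomes the gain exists only if the ANOVA is run on complete cases, which is its classical form but is not stated. If 10% missed each of two follow-up visits independently (an assumption), 1 − 0.9² = 19% would drop out. However, "We plan to enrol 20% more persons to account for dropouts" takes 40 to 48, and 48 × 0.81 is about 39.
- **That the trial is underpowered.** On its own assumptions it is not.

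What survives the reply is that the method is a stated choice, a more precise one is available from the same data, and the treatment contrast is left to the reader.

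**Conclusion.** The point holds as a loss of efficiency plus an unnamed treatment contrast. It is not a bias, and it does not undermine the sample size of 40.

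For two time points the planned test has 2/(1+r) times the variance of ANCOVA: 1.33 times at r = 0.5 and 1.05 times at r = 0.9. At an assumed 0.6 SD, the gain in power runs from about 15 points at r = 0.3 to under 1 point at r = 0.9. The result rests on equal variances, approximate normality and a correlation that the article does not give. The 19% power for the group main effect shows why the test should be named. The article does not say that this term will be used. The change is worth making because it costs almost nothing.

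**What to change.** Amend Data analysis as follows.

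- **Blood and saliva (two time points):** ANCOVA of the week-16 value on group and baseline value.
- **Three-visit outcomes:** a linear mixed model of the follow-up values on group, visit, group-by-visit and baseline value. This keeps participants who miss one of the two follow-up visits.
- **Treatment effect:** name the adjusted week-16 between-group difference with its 95% CI as the basis for statements on efficacy, and report within-group changes descriptively.

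The cost is analysis wording and about one degree of freedom. Both models are available in the SPSS package already named, and no new data are needed. Two matters stay open and need separate treatment: the rule under Program attendance/adherence that leaves out training-group participants below 80% attendance, and the Kruskal-Wallis branch for non-normal outcomes.

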**ASSESSMENTS**								
Fasting blood samples		x					x	
Saliva samples		x					x	
Body composition			x			x		x
Physical fitness			x			x		x
Lung function (Spirometry)			x			x		x
Subjective quality of life			x			x		x
Systolic and diastolic blood pressure	x		x			x		x
Assessment of dietary intake			x					x
Accelerometry		x					x	
**RANDOMIZATION**				x				
Maximal dynamic strength to estimated 1RM				x		x		

^a^ Screen and baseline assessments will be completed within 20 days;

^b^ The exercise sessions will be performed 3 times/week (i.e., Monday, Wednesday, and Friday) over 16 weeks;

^c^ This study includes an intermediate assessment, which will be carried out in the eighth week of intervention;

^d^ Post-testing assessments will be done within 10 days of the last exercise session.

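### Kruskal-Wallis is the only fallback named for the repeated-measures ANOVA; it is wrong for within-group change and, on raw visit values, does not test the group-by-time effect

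*Protocol article*

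**What the plan says.** All of the relevant rules stand in the Data analysis section of the protocol article.

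- Main method: "Assuming data normality, a two-way analysis of variance (ANOVA) for repeated measures will be applied for intra- and inter-group comparisons".
- Check that chooses the branch: "The assumption of normality will be tested using histograms, normal probability plots and Shapiro-Wilk test".
- Fallback: "In absence of normality, non-parametric Kruskall-Wallis test will be used".
- Follow-up: a Bonferroni post hoc "test will be performed if significant differences exist (alpha level set at 0.05").

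The design is a "single-blinded two-arm randomized controlled trial (RCT) with parallel groups, and an allocation ratio of 1:1" (Study design and setting). The same people are measured more than once: "Baseline assessments will be repeated after 8 weeks (mid-testing, visit 5) and upon completion of the intervention (visits 6 and 7") (Outcome measures). Table 3 gives the visits by outcome. The row "Fasting blood samples" and the saliva row are marked at visits 2 and 6 only, so two time points. Lung function and quality of life are marked at visits 3, 5 and 7, so three.

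The section does not say which values Kruskal-Wallis is applied to, and it names no transformation and no paired or repeated-measures rank test.

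**The concern.** A fallback has to answer the same question as the method it replaces. The ANOVA answers two questions: did a group change over time, and did the groups change differently? Kruskal-Wallis asks whether several independent samples come from one distribution. It has no participant effect, uses no baseline and has no interaction. With two groups it is the two-sided Mann-Whitney test.

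The text also leaves open what is compared: the arms at one visit, the arms on a change score, the visits within an arm, or the four group-by-visit cells. These uses behave very differently, and the analyst would choose among them after the normality check. A Bonferroni post hoc has no pairs to adjust when only two arms are compared. It would make sense for a Kruskal-Wallis test over visits or cells, which is where independence fails.

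At stake are the within-group result for any non-normal outcome and a clear definition of its between-group test. Those outcomes may include primary ones.

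**Working it through.** **1. The effect the sample size rests on.** The Estimated sample size section gives effect size 0.30, 20 per group, 95% power, 5% alpha and an F test. Reading 0.30 as Cohen's f, with k = 2 groups, m = 2 measurements and an assumed correlation ρ = 0.5 (not stated in the protocol), the group-by-time interaction has

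λ = f²·N·m/(1−ρ) = 0.09 × 40 × 2 / 0.5 = 14.4, with df 1 and 38, so power = 0.959.

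N = 40 is also the smallest even total that reaches 95%. With m = 3, power at 40 is 0.988. For a pure between-group effect, λ = 0.09 × 40 × 2 / 1.5 = 4.8 and power is 0.57. On these assumptions the stated size is reproduced for a within-participant or group-by-time effect. Kruskal-Wallis on raw visit values does not test the group-by-time effect.

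**2. Why the test misbehaves on repeated values.** Let σ² be the variance at a visit, n the number per arm and r the within-person correlation.

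- *Visits within one arm.* The test takes the variance of the difference between two visit means as 2σ²/n. The true value is 2σ²(1−r)/n. Under no change the rejection rate is about P(|Z| > 1.96/√(1−r)). For r = 0.5, 1.96/0.707 = 2.77, giving 0.6%. For r = 0.7, 1.96/0.548 = 3.58, giving 0.03%.
- *Both readings pooled per arm.* The test takes the variance of an arm mean as σ²/(2n). The true value is σ²(1+r)/(2n). The rejection rate is about P(|Z| > 1.96/√(1+r)). For r = 0.5, 1.96/1.225 = 1.60, giving 11.0%. For r = 0.7, 1.96/1.304 = 1.50, giving 13.3%.

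**3. Simulation for two visits (blood and saliva).** From the protocol: 20 per arm, two arms, two time points, 5% alpha. Assumed: log-normal marker, r = 0.5–0.7, true shift 0.6 SD on the log scale.

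| Use of the test | No effect | True shift of 0.6 SD |
|---|---|---|
| Kruskal-Wallis, pre vs post within an arm | 0–0.8% | about 42% |
| Wilcoxon signed-rank, same comparison | near 5% | 69–89% |
| Kruskal-Wallis, both readings pooled per arm | about 11–13% | – |
| Kruskal-Wallis, post values between arms | 4.4–5.0% | about 44–45% |
| Test of individual log-change between arms | near 5% | 46–67% |
| Baseline-adjusted ANCOVA on logs | near 5% | 56–73% |

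Run on the four group-by-visit cells, Kruskal-Wallis rejects about 56% of the time when both arms shift equally by 0.6 SD. It is then detecting time and not treatment, and its p-value does not tell the two apart.

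**4. Three visits (lung function, quality of life).** With the same assumptions and half of the shift at week 8, within-arm Kruskal-Wallis rejects 0–0.3% under no change. Under the true shift it has 20–24% power, against 50–73% for Friedman. Pooling three readings gives 16–20% false positives. These figures do not apply to the blood and saliva markers.

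**The case against.** Several stronger readings are tempting and should be resisted.

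- *That Kruskal-Wallis cannot compare change between groups.* On one change score per participant it equals Mann-Whitney and keeps its error rate near 5%. The same holds for post values alone. What stands is that the protocol states neither use, and that neither gives a within-group test.
- *That the fallback inflates between-group false positives.* It does so only if repeated readings are pooled as if they came from different people. The protocol does not say that they will be.
- *That it loses much of the between-group power.* The planned ANOVA interaction with two visits is a test of change. At r = 0.5 that test has 46% power, against 44–45% for Kruskal-Wallis on post values, which is almost no loss. The loss is real at r = 0.7 (67%), but the documents give no correlation. ANCOVA is not the planned method.
- *That within-group change would almost never be found.* The near-zero rates are for no change. With a true shift and two visits, power is about 42%.
- *That most primary biomarkers would take this branch.* Concentrations bounded at zero are often skewed, but the protocol reports no distributions.
- *That Shapiro-Wilk alone decides.* Histograms and normal plots are named alongside it.

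It can also be said that a condensed article leaves detail to a full plan, and that the plainly invalid use is not the randomised comparison and errs on the conservative side. The second part lowers the severity. The first does not remove the point: the article names a specific test for a stated purpose, within-group comparison included, and that test does not serve it.

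**Conclusion.** The stated fallback is wrong as written for within-group comparisons, and the between-group use is left undefined. This follows from the structure of the test and depends on no assumed figure.

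The size does rest on assumptions: a correlation of 0.5–0.7, a log-normal marker and a 0.6 SD shift. On these, for two visits, the within-group test loses between 69 − 42 = 27 and 89 − 42 = 47 percentage points of power against signed-rank. The consequence between groups runs from none (one value per participant, at r = 0.5) to a misleading result (four cells, or pooled readings), depending on a choice that the protocol does not make. How many outcomes are affected cannot be known from the document.

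This is a should-fix point: a conditional branch, with its clearest failure outside the randomised comparison, and cheap to correct.

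**What to change.** Replace the fallback sentence with wording such as:

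> In absence of normality, outcomes will be log-transformed where this is suitable and analysed with the planned repeated-measures model. If the transformation fails, groups will be compared by the Mann-Whitney test on each participant's change from baseline (or by rank ANCOVA adjusting for baseline), and within-group change by the Wilcoxon signed-rank test (two visits) or the Friedman test (three visits), with Bonferroni-adjusted pairwise follow-up.

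This keeps the planned model as the first choice and gives each question a test that fits it. One of the two between-group options should be fixed before the data are seen. The cost is a wording change; no participants, visits or measurements are added, and the methods are available in the SPSS package already planned.
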